**Methods:**

Thirty-nine hypertensive volunteers aged 35 to 55 years will be randomly assigned to two exercise sessions: AE (40 min on a cycle ergometer at 60% of HR reserve), RE (4 lower limb sets with 12 repetitions at 60% 1-RM for 40 min), or CE (RE for 20 min + AE for 20 min). Each exercise group will be randomized to receive either an α1-adrenergic blocker (doxazosin 0.05 mg/kg^−1^) or placebo. Ultrasound measurement of FMD is performed 10 min before and 10, 40, and 70 min after exercise. ANS activation is monitored using a Finometer and measurements are taken during 10 min before each FMD assessment. Arterial stiffness is assessed by pulse wave velocity (PWV) analysis using a Complior device.

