## Methods/design

### Study setting

This is a randomized, double-blind (blinded to the drug/placebo but not to the type of exercise) parallel-group exploratory clinical trial with a group allocation rate of 70% for the calculated sample. Our study was approved by the local ethics committee (#5678/19) and it will be conducted at Instituto de Cardiologia do Rio Grande do Sul/Fundação Universitária de Cardiologia (ICFUC) – study site. We will use radio, television, social media advertisements to recruit volunteers as well as invitations through phone calls to eligible individuals following a review of medical records from the hospital where the study will be held. All eligible individuals must read and sign a free and informed consent (supplementary material) before entering the study. The study protocol is being developed following the principles of the Declaration of Helsinki. All study information is confidential; volunteers’ names will be kept confidential and all data obtained in the study will be used for academic purposes only. Research data will be stored for five years and then discarded according to the guidelines of CNS Resolution No. 466/12. Finally, any adverse effect during the research will be reported to the local ethics committee that will have access to the adverse results and will make the decision in relation to terminating the study, if applicable. Relevant protocol amendments such as changes to eligibility criteria, unwanted effects, violation of the rights of volunteers, registration, and analysis of results as well as contributions of the study investigators will be reported to the research project coordinator ([name]) and then to the local ethics committee. The study protocol will be updated in the clinical trial registry if applicable.

The study will not receive financial support from any institution, including from ICFUC. Also, ICFUC was not involved in the study design and will not be involved in either data collection, management, analysis, and interpretation or manuscript writing and any decisions regarding submission of articles for publication.

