### Eligibility criteria

Recruitment will be through on-site screening, media postings, and patient databases. Thus, hypertensive male and female individuals aged 35 to 55 years receiving health care at the study site, using anti-hypertensive drugs, who do not engage in regular physical exercise (≥ 2 sessions per week) are eligible to participate. Exclusion criteria are individuals with diabetes mellitus; chronic renal failure; body mass index (BMI) ≥ 35 kg/m^2^; coronary artery disease; heart failure; users of beta-blockers and/or alpha-blockers; smoking; lower limb injuries that prevent them from engaging in the study intervention; and females aged 35 to 55 with menopause. If doxazosin induces a change in exercise workload or a reduction in blood pressure to levels that would affect exercise performance, the volunteer will be excluded from the study. If a volunteer drops out before completing both study interventions (α1-adrenergic blocker or placebo), we will make an effort to reach them and find out the reasons behind it. If their decision is final, it will be considered “subject withdrawal” and their data will be excluded from the final analyses.

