### Sample size

The sample size is calculated according to Atkinson et al. [26]. In their study, they compared endothelium-dependent vasodilation (by FMD) after a single session of moderate-intensity AE for 30 min in healthy individuals receiving an α1-adrenergic blocker (prazosin 0.05 mg/kg^−1^) or placebo and reported a *difference in means of* 3.1% with standard deviations (SDs) of 1.13% for placebo and 1.91% for prazosin. For finding a similar difference in FMD (3.1%) between these two conditions (α1-adrenergic receptor block versus placebo) after our protocol’s exercise session (AE, RE, and CE) considering *α* = 0.05 and 80% power, a sample of five volunteers per group (*n* = 15) is required.

For a comparison of FMD measurements among exercise types (AE, RE, and CE), our sample calculation is based on pre-exercise SD (1.18%) and post-exercise SD (1.91%) for the prazosin group as described by Atkinson et al. Thus, to find a difference in FMD of 1.62% considering *α* = 0.05 and 80% power, a sample of 10 individuals per group (*n* = 30) is required. Assuming a 30% loss, a sample of 39 individuals would be required (*n* = 13 per group).

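### The allowance for 30% loss is computed as 30 × 1.3 = 39, which covers a loss of only 23%; at 30% loss about 27 volunteers remain, not the required 30

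*Protocol article*

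**What the plan says.** The Sample size section of the protocol article gives two requirements. For α1-blocker versus placebo it asks for five volunteers per group, 15 in total. For the comparison among aerobic, resistance and combined exercise it is set "to find a difference in FMD of 1.62% considering *α* = 0.05 and 80% power", and concludes that "a sample of 10 individuals per group (*n* = 30) is required". The second requirement is the larger and drives enrolment. The allowance for loss follows directly: "Assuming a 30% loss, a sample of 39 individuals would be required", given as 13 per group. The Methods paragraph of the abstract uses the same figure as the planned enrolment: "Thirty-nine hypertensive volunteers aged 35 to 55 years will be randomly assigned".

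Two other sections settle what happens to lost volunteers. Under Eligibility criteria, for anyone who withdraws before completing both the blocker and the placebo session, "their data will be excluded from the final analyses". The Statistical analysis section specifies a per-protocol analysis.

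**The concern.** A loss rate is a fraction of those enrolled. To finish with a required number, one divides that number by the fraction expected to remain. The protocol multiplied by one plus the loss rate, which always gives too small a figure, and the gap widens as the rate rises. At 30% it is large enough to see in a trial of this size.

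Because the analysis set contains completers only, every loss comes straight off the analysed number. If the stated loss occurs, the trial misses the sample size that the same paragraph calls required. What is at stake is the accuracy of a figure by which readers and the ethics committee judge the trial, and a few points of power for one of its two planned comparisons.

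**Working it through.** **Inputs, all from the Sample size section:** required completers 30 (10 per group, three groups); loss 30%; stated enrolment 39 (13 per group); α = 0.05; power 80% at 10 per group.

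**1. Reproducing the stated figure.** n × (1 + d): 30 × 1.3 = 39, and 10 × 1.3 = 13. Both match exactly, so this is how 39 was obtained.

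**2. What remains at the stated loss.** 39 × (1 − 0.30) = 27.3, about 27 in total. Per group, 13 × 0.70 = 9.1, about 9. The shortfall against 30 is 3 volunteers (3/30 = 10%), or one per group.

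**3. The loss that 39 can absorb.** (39 − 30)/39 = 9/39 = 23.1%.

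**4. The inflation that matches the premise.** n/(1 − d): 30/0.70 = 42.9, so 43; check, 43 × 0.70 = 30.1. Rounding up within groups, 10/0.70 = 14.3, so 15 per group or 45; check, 15 × 0.70 = 10.5.

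**5. Effect on power for the comparison among exercise types.** Take the protocol's 80% at 10 per group as given and assume a two-sided test (sidedness is not stated). By normal approximation, 80% power corresponds to a standardised effect of 1.96 + 0.84 = 2.80, which scales with √n. At 9 per group: 2.80 × √(9/10) = 2.66; 2.66 − 1.96 = 0.70; power = Φ(0.70) ≈ 75.7%. Anchoring a two-sample t-test at 80% for 10 per group gives 75.1% at 9. The cost is between 4 and 5 points.

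**6. Blocker versus placebo.** The stated need is 5 per group, and 9 per group exceeds it. With that comparison's inputs (difference 3.1%, SDs 1.13% and 1.91%), a two-sided independent t-test at 9 per group has power of about 97.5%. The choice of test is an assumption.

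**7. How likely the shortfall is.** If each volunteer were lost independently with probability 30% (an assumption), the chance that at least 30 of 39 remain would be about 22%.

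**The case against.** The arithmetic is hard to dispute; the case on the other side concerns its weight. The shortfall is about one volunteer per group and arises only if losses exceed 23%. The document gives no source for the 30%, which looks like a planning guess, and the Study setting section calls the trial exploratory. The primary objective in Table 1 compares blocker with placebo, and the number stated for that comparison is comfortably met. All of this stands and keeps the point minor. One limit applies: the primary objective refers to sessions of different exercise types, so the comparison among types is not irrelevant.

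A reader might infer something stronger in three ways.

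- **That power falls to 53%.** The SDs quoted are "pre-exercise SD (1.18%) and post-exercise SD (1.91%) for the prazosin group". Their root mean square, √((1.18² + 1.91²)/2) = 1.59, in a two-sided independent t-test for a difference of 1.62%, gives 57.9% at 10 per group and 53.0% at 9. The document does not name that test. A paired pre/post calculation gives 10 at an assumed correlation of about 0.6, also unstated. Most of the gap between 80% and these figures lies in how the base of 10 was derived. The loss allowance accounts for only the last few points.
- **That enrolment must rise to 45.** That figure supposes equal groups, but the Randomization and blinding section specifies simple randomisation, which does not guarantee them. The direct correction is 43, and the statement can be put right without enrolling more.
- **That the 70% in the Study setting section confirms the 30% loss.** The phrase about group allocation there is unclear, and nothing here rests on it.

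**Conclusion.** The statement that 39 volunteers cover a 30% loss is wrong as written, and the error is minor. At that loss about 27 volunteers (9 per group) remain against a stated need of 30 (10 per group); 39 covers a loss of 23%. No other section repairs this, since withdrawals are dropped and the analysis is per protocol.

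The counts rest only on the protocol's own figures. The power estimate of about 75–76% for the exercise-type comparison additionally assumes that the stated 80% at 10 per group is right and that the test is two-sided. The document does not support reading this as a threat to the whole trial: the number stated for blocker versus placebo is still exceeded.

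**What to change.** Keep 39 and amend one sentence in the Sample size section, in one of two ways:

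- state that 39 allows for a loss of 23%; or
- keep the 30% and state that about 27 volunteers (9 per group) would then remain, with the power for the comparison among exercise types restated at 9 per group using the test and SD behind the original 10.

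Neither needs extra recruitment. The only cost is a slightly less favourable statement of loss tolerance or power. If 30 completers after a 30% loss is what the investigators intend, the enrolment figure would have to read 43 (45 with equal groups), and the abstract would need the same change.

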### Randomization and blinding

Randomization of the study interventions (exercise groups) as well as assignment to intervention conditions (either an α1-adrenergic blocker or placebo) are carried out *using computer program* (www.randomization.com) with a coded numeric distribution. Allocation concealment is guaranteed by using sealed envelopes; the random allocation of volunteers is kept in an inaccessible place and researchers will not have a priori knowledge of the intervention assignment to each volunteer. Randomization is carried out by an independent researcher not involved with the study.

Considering the volunteers’ age group (35 to 55 years) and that comparison analyses (primary and secondary outcomes) involve testing for baseline differences, we are conducting simple randomization divided into two steps: (1) by exercise type (AE, RE, or CE) and (2) the order of condition (either placebo or α1-adrenergic blocker). All volunteers are blinded to the intervention allocation and will only have access to this information after a baseline evaluation. They are also blinded to the intervention condition (either placebo or α1-adrenergic blockade). The researchers responsible for the analyses of data are blinded to the intervention allocation and condition to minimize potential measurement bias. As the medical staff and investigators are not blinded, unblinding will not occur.

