## Introduction

Endothelial dysfunction precedes atherosclerosis [1]. Endothelial cells play an important role in modulating vascular angiogenesis and vascular tone and permeability and mediating inflammatory responses and homeostasis [2]. This function of vascular protection is largely attributed to nitric oxide endothelial synthase, an enzyme responsible for nitric oxide (NO) synthesis in the vascular endothelium [2].

Endothelial dysfunction is characterized by a reduction of local NO bioavailability and/or insufficient vasomotor response that occur in certain conditions including arterial hypertension [3], diabetes mellitus [4], obesity [5], dyslipidemia [6], metabolic syndrome [7], aging [8], menopause [9], and sedentary lifestyle [10]. Flow-mediated dilation (FMD) of the brachial artery is an indirect non-invasive technique to assess endothelial function and is chiefly dependent on *NO availability* [11]. Since a*cute* post-*exercise changes in vascular function* may also predict long-term adaptations [12] the acute response to exercise has been widely studied [3, 13].

Lifestyle changes including regular physical exercise are recommended as part of the therapeutic approach for hypertension management [14, 15]. Factors most commonly associated with potential antihypertensive effects and chronic post-exercise changes in endothelial function include reduced autonomic nervous system (ANS) activation [16], balance between vasodilators and vasoconstrictors [17], and reduced levels of the vasoconstrictor endothelin-1 (ET-1) [18].

A meta-analysis that examined cardiovascular risk factors and/or factors associated to established cardiovascular disease found that aerobic and resistance training can potentially improve FMD of the brachial artery [19]. Our research group also found an improvement of 1.45% (95% CI − 0.11 to 3.00) in FMD in response to aerobic training in hypertensive individuals [20]. This finding is clinically relevant as a 1% increase in FMD is correlated to ~ 13% risk reduction of major cardiovascular outcomes [21].

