### Statistical analysis

A per-protocol (PP) analysis will be conducted. The Shapiro-Wilk is used to test the normality of data. Values are presented as means ± standard deviations or medians and 95% confidence intervals (95% CIs) according to the distribution of variables. A multivariate analysis of data is performed using the generalized estimation equations (GEE) for repeated measures with Bonferroni’s post hoc. Pearson’s and Spearman’s tests are used to assess potential correlations between variables according to their distribution. Statistical analyses are carried out using the Statistical Package for Social Sciences (SPSS) 24.0. A level of significance of < 0.05 is set for all analyses.

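### Baseline testing is a weak reason for simple randomisation: if between-group tests are meant, 9 to 13 volunteers per exercise group would miss a true 0.5-SD difference about 77–83% of the time

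*Protocol article*

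**What the plan says.** In the protocol article, Randomization and blinding gives two reasons for simple randomisation. One is the age range: "Considering the volunteers’ age group (35 to 55 years". The other is that "comparison analyses (primary and secondary outcomes) involve testing for baseline differences, we are conducting simple randomization divided into two steps". The first step allocates exercise type, so AE, RE and CE are different people. The second is "2) the order of condition (either placebo or α1-adrenergic blocker", so each volunteer receives both conditions.

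Sample size sets the exercise-type comparison at "80% power, a sample of 10 individuals per group" and then states: "Assuming a 30% loss, a sample of 39 individuals would be required". Eligibility criteria removes withdrawals from the final analyses, and Statistical analysis plans a per-protocol analysis by GEE for repeated measures with Bonferroni post hoc tests. On the threshold it says: "A level of significance of < 0.05 is set for all analyses".

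The Introduction lists conditions that go with endothelial dysfunction, among them "obesity [5], dyslipidemia [6], metabolic syndrome [7], aging [8". Age (35 to 55 years) and BMI (below 35 kg/m²) can still vary within the eligibility limits.

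**The concern.** Baseline testing can justify leaving allocation unrestricted only if the test would reveal an imbalance worth worrying about. In groups this small it mostly would not, so a non-significant result says little about whether AE, RE and CE started level.

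At stake is the one comparison made between different people. If the groups differ by chance in pre-exercise FMD or in something related to it, that difference can carry into the AE/RE/CE result. How much is carried depends on whether and how the analysis uses the pre-exercise value.

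**Working it through.** **Inputs from the protocol article.** 10 per exercise group, 30% loss, 39 in total, α = 0.05, target difference 1.62% FMD, SD 1.18% before and 1.91% after exercise (all from Sample size, with α also in Statistical analysis).

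**Assumptions made here.** Two-sided tests; a relevant imbalance of 0.5 SD; pre–post correlation r of 0.3, 0.5 or 0.7.

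**Group sizes.** The stated total reproduces as 30 × 1.3 = 39, or 13 per group. A 30% loss from 13 leaves 13 × 0.7 = 9.1. The range is therefore 9 to 13 per group. It is a favourable range: under truly unrestricted allocation of 39 people, an exact 13/13/13 split occurs in only about 2% of allocations.

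**Step 1: miss rate of a baseline t test.** Non-centrality λ = 0.5 × √(n/2), with 2n − 2 degrees of freedom. The smallest observed gap that reaches significance is t(0.975) × √(2/n), in SD units.

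| n per group | λ | Power | Missed | Smallest significant gap |
|---|---|---|---|---|
| 9 | 1.061 | 17.0% | 83.0% | 1.00 SD |
| 10 | 1.118 | 18.5% | 81.5% | 0.94 SD |
| 13 | 1.275 | 23.2% | 76.8% | 0.81 SD |

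A three-group F test with one group shifted by 0.5 SD misses it about 84%, 82% and 77% of the time. About 63 per group would be needed for 80% power at 0.5 SD. The result depends on the assumed size: 0.3 SD is missed about 89–91% of the time, 0.8 SD 50–64%, and 1.0 SD 31–49%.

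**Step 2: how often chance produces such gaps.** In simulation, at least one pair among the three groups differs by more than 0.5 SD on a given baseline variable in 54%, 50% and 41% of randomisations at n = 9, 10 and 13.

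**Step 3: effect on the exercise-type contrast (two groups of 10).** Take trials where the pre-exercise gap is at least 0.5 SD but the test is not significant. In simulation the average gap g in these trials is about 0.66 SD. The expected shifts in % FMD are:
- post-exercise values alone: r × 1.91 × g
- change from pre-exercise: (r × 1.91 − 1.18) × g
- adjusted for pre-exercise FMD: about 0

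| r | Post-only | Change from pre | Adjusted |
|---|---|---|---|
| 0.3 | 0.573 × 0.66 = 0.38 | (0.573 − 1.18) × 0.66 = −0.40 | about 0 |
| 0.5 | 0.955 × 0.66 = 0.63 | (0.955 − 1.18) × 0.66 = −0.15 | about 0 |
| 0.7 | 1.337 × 0.66 = 0.88 | (1.337 − 1.18) × 0.66 = +0.10 | about 0 |

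Direct simulation agrees with these values. Against the 1.62% target, the post-only shift is 0.38/1.62 = 23% to 0.88/1.62 = 54%. The change-from-pre shift is at most 0.40/1.62 = 25%.

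**Step 4: precision.** Simulated power for 1.62% with 10 per group is about 53% for change from pre and 52% for adjustment at r = 0.5, and 70% and 68% at r = 0.7. At r = 0.3 both are about 43–45%. A change analysis thus loses little or no power here; what adjustment adds is the removal of the conditional shift whatever r turns out to be.

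**The case against.** A reader might infer that the trial will declare AE, RE and CE equivalent once a baseline test is non-significant. The article does not say so. Its phrase is attached to the outcome analyses, and FMD is measured before and three times after exercise, so it may mean comparison with the pre-exercise value. That reading is plausible, which is why the point is conditional. It does not rescue the rationale, though: comparing with one's own pre-exercise value is no reason for leaving allocation unrestricted either.

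A reader might also take the post-only shift (about 0.6% FMD at r = 0.5) as the expected error, or assume a rule of adjusting only when the baseline test is significant, which holds power to about 43% against 52% with routine adjustment. The article states neither a post-only comparison nor such a rule. A GEE that compares change from pre-exercise does about as well as adjustment on power, with a smaller conditional shift.

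Three further points stand. Under concealed random allocation there is no systematic difference to detect; chance imbalance is already allowed for in the overall type I error and confidence intervals, so the issue is conditional error and what a non-significant test can show. A covariate list is commonly left to the full protocol or analysis plan, so its absence from this article is not the fault. And the trial is labelled exploratory, with its primary objective in Table 1 being the blocker-versus-placebo comparison, which imbalance between exercise groups does not bias because each volunteer has both conditions.

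**Conclusion.** The point holds in a limited form. Baseline testing is given as a reason for simple randomisation and cannot bear that weight if between-group tests are meant: the miss rate is about 77–83% for a true 0.5-SD difference at 13 to 9 per group. The 0.5 SD and the two-sided test are assumptions, with the range shown above.

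The consequence is confined to the AE/RE/CE contrast. It runs from about zero (adjusted), through −0.4 to +0.1% FMD (change from pre), to 0.4–0.9% FMD (post-only), for r between 0.3 and 0.7. The SDs are those the protocol borrows from healthy volunteers on prazosin. The documents do not support a claim that the primary result is biased or that the trial will misuse a non-significant test. This is a worthwhile correction of a rationale and a model, not a threat to the main comparison.

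**What to change.** 1. In Randomization and blinding, remove baseline testing as a reason for simple randomisation. Describe baseline characteristics by exercise group without p-values.
2. In Statistical analysis, prespecify for the AE/RE/CE contrast a model of post-exercise FMD at 10, 40 and 70 min. It should always adjust for pre-exercise FMD and for one fixed covariate already collected, age, whatever the baseline p-values. Report the adjusted contrasts with 95% CIs.
3. Restrict that adjustment to the exercise-type model. The tablet is taken 90 min before exercise and FMD is measured 10 min before it, so the pre-exercise value comes 90 − 10 = 80 min after the tablet. It is a valid baseline for exercise type but not for the drug; in a model that also estimates blocker versus placebo it could absorb part of the primary effect. Fit the exercise-type model within each condition, or use the volunteer's mean pre-exercise FMD over both sessions, and state in advance which.

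The cost is wording, a separate model and one or two degrees of freedom from 27 to 39 volunteers. With so few clusters, GEE standard errors need care in any case. No new measurement is needed.

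### Simple randomisation of 39 volunteers does not deliver the planned 13 per exercise group, and leaves about a one-in-three chance that some group starts below the 10 needed to compare exercise types

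*Protocol article*

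**What the plan says.** The protocol article, under Randomization and blinding, states: "we are conducting simple randomization divided into two steps". Step one assigns the exercise type (aerobic, resistance or combined). Step two assigns the order in which the volunteer receives placebo and the α1-blocker. No block, stratum or other restriction is mentioned. The reasons given are the volunteers' age range and that the comparisons "involve testing for baseline differences".

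Under Sample size there are two calculations. The α1-blocker versus placebo contrast needs five volunteers per group (15 in total). The comparison among exercise types needs "a sample of 10 individuals per group" (30 in total). The second calculation sets the enrolment: "Assuming a 30% loss, a sample of 39 individuals would be required", which is 13 per group.

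Under Eligibility criteria, the data of volunteers who withdraw before completing both conditions are dropped from the final analyses. Under Statistical analysis, the analysis is per protocol.

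**The concern.** The sample size is fixed group by group, but the allocation method does not fix group sizes. With only 39 volunteers and three groups, chance variation in the counts is large compared with the margin between 13 planned and 10 needed. A group that starts small cannot recover, because withdrawals are removed from the analysis. At stake is the precision of the comparison among exercise types, and whether the allowance for loss exists in every group.

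The same applies to the second step. Nothing keeps the number of drug-first and placebo-first volunteers close to equal within an exercise type. If FMD differs systematically between the first and second session, an uneven split carries part of that difference into the unadjusted drug-placebo contrast.

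The stated reasons do not bear on either problem. A narrow age range does not control group size or order. Nor does testing for baseline differences, if that means testing between groups.

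**Working it through.** **Inputs from the protocol article.** 39 randomised; three exercise types; two condition orders; 13 per group planned; 10 per group required for the exercise-type comparison and five for the drug-placebo contrast; difference of 1.62% FMD; SDs 1.18% and 1.91%; α = 0.05; 30% loss.

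**Assumptions.** Probability 1/3 for each exercise type (implied by 13 per group), 1/2 for each order, two-sided tests, and loss independent between volunteers.

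**The plan's own figure.** 10 × 1.3 = 13 per group, and 3 × 13 = 39. The stated total is reproduced. The 10 per group is taken as given here.

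**Group sizes at allocation.** Under simple randomisation the counts (a, b, c) have probability 39!/(a! b! c!) × (1/3)^39. Summing exactly over all splits:
- P(13/13/13) = 39!/(13!)³ / 3^39 = 0.021.
- P(smallest group below 10) = 0.340. For one named group it is 0.115.
- P(smallest group 10 or fewer) = 0.568. More often than not, some group has no room for loss when allocation ends.
- Expected smallest group = 10.0; mean gap between largest and smallest = 6.1; P(gap of 8 or more) = 0.312.
- P(smallest group below 5), the requirement for the drug-placebo contrast, = 0.0026.

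**Completers after loss.** Chance that at least one group ends with fewer than 10 completers:

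| Assumed loss | Simple randomisation | Fixed 13 per group |
|---|---|---|
| 0% | 34% | 0% |
| 10% | 62% | 10% |
| 20% | 87% | 58% |
| 30% (planned) | 98% | 93% |

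The last row follows from 13 × 0.7 = 9.1 expected completers per group, already below 10.

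**Power cost of unequal groups alone.** Two-sample t test, difference 1.62, noncentrality 1.62 / (SD × √(1/n₁ + 1/n₂)):
- SD 1.18: 13 v 13 gives 0.919; 9 v 15 gives 0.875.
- Pooled SD √((1.18² + 1.91²)/2) = 1.59: 13 v 13 gives 0.704; 9 v 15 gives 0.638.

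**Condition order.** Taking 13 in a group, P(split of 3:10 or worse) = 2 × (1 + 13 + 78 + 286)/2^13 = 756/8192 = 0.092. Over three groups, 1 − (1 − 0.092)³ = 0.252. In a group split 3:10, the unadjusted mean drug-placebo difference contains (10 − 3)/13 = 0.54 of any difference between sessions; with 6:7 it contains (7 − 6)/13 = 0.08.

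**The case against.** Several stronger readings are tempting, and the document does not support them.

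- **That the primary comparison has a one-in-three chance of being too small.** It does not. The primary objective is α1-blocker versus placebo, sized at five per group, and the chance of any group starting below five is 0.26%. The 34% belongs only to the exercise-type comparison.
- **That unequal groups invalidate the trial.** Simple randomisation is unbiased whatever the counts. The cost is power, and 0.704 to 0.638 (or 0.919 to 0.875) is modest in a trial that calls itself exploratory.
- **That blocking would secure 10 completers per group.** At the plan's own 30% loss it would not (93% v 98%). That shortfall comes mainly from how the loss allowance was calculated, which is a separate matter.
- **That uneven order biases the drug effect.** Each volunteer receives both conditions, and random order keeps the contrast unbiased in expectation. Imbalance matters only if there is a period or carry-over effect, which the article does not show. A period term could be in an analysis plan not seen here. The 25% also assumes exactly 13 in each group.
- **That baseline significance tests are offered as a remedy for imbalance.** The phrase may instead mean comparing post-exercise FMD with pre-exercise values. It is unclear, which calls for clarification.

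Predictability is a fair objection to small fixed blocks, since exercise type is open and there is one site. Concealed varying blocks, or one permuted list of 39, largely answer it. Some volunteers may also already be allocated, so a wholly new list may not be possible.

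What stands after all this is the mismatch itself: the stated method does not produce the stated group sizes. If the term simple was used loosely and the list does fix 13 per group, the description is wrong and still needs correcting.

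**Conclusion.** The concern holds for the exercise-type comparison and the planned group sizes. Under the stated method, with equal probabilities assumed, the planned 13/13/13 is reached 2% of the time, and at least one group starts below the required 10 in 34% of trials, before any loss. The drug-placebo contrast is hardly affected in size. The harm is a modest loss of power and a loss allowance that is not secured in each group; it is not bias. The benefit of restricted allocation depends on loss: large at 10% (62% down to 10%) and small at the planned 30% (98% down to 93%). Balancing the order is a cheap protection against a possible period effect, not the repair of a demonstrated one. The change should be made, but the trial does not fail without it.

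**What to change.** For volunteers not yet allocated, replace simple randomisation with a concealed restricted list. Either use permuted blocks of varying size for exercise type, or one randomly permuted list fixed at 13 per type. Block the condition order within exercise type, so that a group of 13 splits about 6:7 and any period effect is close to balanced between drug and placebo. If some volunteers are already allocated, say how many and how the new list takes account of them. If the existing list already fixes 13 per group, correct the description instead.

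State what testing for baseline differences means, and either explain how it and the age range bear on the allocation method or delete that rationale.

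The cost is small: the independent researcher, computer-generated list and sealed envelopes are already in place, and the article reports that research at the site is suspended, which leaves time before resumption. The downside is slightly greater predictability of an open exercise allocation, limited by undisclosed varying blocks or the single 39-slot list. The loss allowance needs separate attention, because restricted allocation alone does not bring 10 completers per group at 30% loss.
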